## Abstract

**Background:**

Regular participation in some type of physical activity brings improvements in health indicators such as cardiorespiratory fitness, muscle strength, and body composition. However, despite evidence indicating health benefits, 1 in 4 adults is physically inactive, a situation that also occurs in the university population. Walking is a physical activity modality that can be easily incorporated into daily activities; therefore, using a walking-based physical activity intervention could improve some health indicators.

**Objective:**

This protocol aims to analyze the impact of a walking-based physical activity intervention on health indicators in university students.

**Methods:**

An intervention group (n=99) and a control group (n=99) will be randomly selected. All participants will be assessed at the beginning and end of the intervention for indicators of health, cardiorespiratory fitness, muscle strength, and body composition. The intervention group will participate in a 14-week walking program with individualized daily goals, self-monitoring, personalized feedback, and weekly educational material, while the control group will only record their steps without receiving personalized goals or feedback.

**Results:**

The recruitment process will begin in March 2026. Initial assessments are scheduled to take place from March 2, 2026, to March 13, 2026. The intervention will be performed from March 16, 2026, to June 19, 2026 (14 weeks). From June 22, 2026, to July 6, 2026, the final evaluations will be performed. The final results of this study are expected to be published by October 2026.

**Conclusions:**

This protocol proposes a novel and feasible approach to overcome common barriers to physical activity in university students, with the potential for large-scale application in similar contexts.

**Trial Registration:**

ClinicalTrials.gov NCT06580769; https://clinicaltrials.gov/study/NCT06580769

**International Registered Report Identifier (IRRID):**

PRR1-10.2196/83983

## Introduction

### Background

Regular participation in some form of physical activity brings a variety of benefits to those who engage in it [1], including improvements in health indicators, such as cardiorespiratory fitness [2,3], muscle strength [4,5], and body composition [6]. However, despite evidence demonstrating its benefits, 1 in 4 adults is physically inactive [7], as they do not meet the recommended duration of 150 to 300 minutes of moderate physical activity per week or 75 to 150 minutes of vigorous physical activity [8]. Among the elements that explain this situation are motivation, access to sports centers, or the support of family or society, which ultimately lead to adults avoiding participation in physical activity [9,10]. In the university population, the situation is similar, as academic pressure is added to other obligations inherent in their lives, resulting in the adoption of unhealthy habits [11,12]. Thus, evidence shows that university students spend 9.82 hours a day in a sedentary state (a value that has been increasing over the last 10 years), which is considerably higher compared to the general population of young adults, a situation that is associated with a higher risk of harmful health outcomes [13].

One means that has been shown to be useful in increasing participation physical activity interventions [14] have been shown to be useful in increasing participation in physical activity and thus reducing health risks, with the most promising being personalized interventions [15]. One option is the measurement of the number of daily steps—a method that has been shown to have the potential to cause increases in physical activity because it is a modality that can be easily incorporated into daily activities [16]—being a valid alternative to meet physical activity recommendations because evidence suggests that moderate to vigorous intensity physical activity recommendations can be achieved, on average, with a total volume of 10,000 steps/d for adults [17]. Recent research implementing physical activity interventions based on daily step measurement has used wearable daily step trackers as a means of monitoring, as they have the facility to allow users to use them in conjunction with mobile phones, allowing them to immediately track their activity and thus manage their time to improve their health [18]. Thus, physical activity interventions based on daily step measurement have been implemented in university students using step trackers, which have demonstrated increases in minutes per day of moderate to vigorous intensity physical activity [19,20]. However, despite having been shown to be efficient in increasing participation, most studies are short term, usually lasting 7 days [21], and studies using longer periods are still limited in terms of evidence on their efficacy [22,23].

As can be seen and as explained by Preusse et al [24], measuring daily steps can provide support to those looking to increase their levels of physical activity. Step trackers are a recommended choice because they are inexpensive and easy to use and provide personalized, ongoing support [16].

Given that adults exhibit low compliance with physical activity recommendations, in particular the university population, which is in a period where daily time is prioritized in their academic activities, the performance of a physical activity intervention based on increasing the number of daily steps and monitored through step trackers represents a potential way to overcome the barriers that hinder the practice of physical activity. In addition, given that the use of this technology provides personalized support, it is reasonable to hypothesize that performing a physical activity intervention that increases the number of daily steps could improve some health indicators.

### Objective

The objective of this study is to provide a working methodology that allows for the analysis of the impact of a walking-based physical activity intervention on health indicators in university students.

## Methods

### Design

It will be a 2-arm randomized controlled trial (RCT) to analyze a physical activity intervention in college students for 14 weeks. The RCT will be reported according to the CONSORT (Consolidated Standards of Reporting Trials) statement [25] and the SPIRIT (Standard Protocol Items: Recommendations for Interventional Trials) guidelines [26] (Multimedia Appendix 1).

### Participants

Participants will be gathered from the Universidad Autónoma de Chile across the campuses located in the cities of Santiago, Talca, and Temuco. Information about the intervention will be disseminated through institutional email, social networks, and informative posters. The following inclusion criteria will be considered: (1) be a university student with active enrollment at the Universidad Autónoma de Chile, (2) aged between 18 and 25 years, (3) have medical consent that authorizes the regular practice of physical activity, and (4) sign an informed consent form to participate in the study. The exclusion criteria will be as follows: (1) having a physical or mental impediment that prevents or limits the performance of physical activity and (2) belonging to special groups, such as professional athletes or pregnant women. The evaluations at the beginning and end of the study will be performed at the university’s facilities using the equipment available at each of the respective campuses (Santiago, Talca, and Temuco).

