### Randomization

This study will adopt a single-blind RCT design. Using EPIDAT software (version 4.2; Pan American Health Organization), participants will be divided into 2 groups (ie, group 1 [intervention] and group 2 [control]).

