#### Upper Body Muscle Strength

Using a digital dynamometer (Takei T.KK.5401; Takei Scientific Instruments Co, Ltd), grip strength will be evaluated. For each hand, the average of 2 measurements will be calculated.

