### Covariables

Before the start of the intervention, sociodemographic variables will be collected through a questionnaire, including questions on age, sex, career, means of transport, geographic area of residence, screen time, and socioeconomic level of the participants.

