### Statistical Analysis

The normality of the data will be checked through the Kolmogorov-Smirnov test, which will indicate the steps to be taken in relation to the comparison tests. Once the pretest tests have been performed, comparison analyses will be performed between groups (2-tailed Student *t* test or Mann-Whitney *U* test) to check the homogeneity of the groups. At the conclusion of the final evaluations of the study, intragroup differences will be analyzed using a statistical test of repeated measures (Student *t* test for related samples or Wilcoxon signed-rank test), along with the intergroup differences (Student *t* test or Mann-Whitney *U* test).

Cohen *d* will be used to determine the effect size on variables in which significant differences are found, using the following scale: 0.2 or greater=small, 0.5 or greater=moderate, and 0.8 or greater=large [33]. In addition, regression analyses will be performed incorporating the covariates. The simple imputation method will be used for all analyses [34], keeping the participants in the group to which they were assigned (intervention or control) regardless of the sessions they attended [35]. In valid cases, analyses will be performed to determine sensitivity [36]. For all tests, statistical significance will be set to *P*<.05. The data will be analyzed using SPSS statistics (version 29; IBM Corp).

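### Outcomes are measured at three campuses, but the stated between-group test is unadjusted and campus is not among the listed covariates, which costs some precision and leaves chance campus imbalance uncorrected

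*Protocol article*

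**What the plan says.** All places are in the Methods of the protocol article.

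- **Participants.** Students are recruited "across the campuses located in the cities of Santiago, Talca, and Temuco". The evaluations at the beginning and end take place on university premises, "using the equipment available at each of the respective campuses".
- **Randomization.** EPIDAT 4.2 is named, and "participants will be divided into 2 groups (ie, group 1 [intervention] and group 2 [control"]). Neither stratification nor blocking is mentioned, and neither is excluded.
- **Covariables.** A questionnaire collects sociodemographic variables, "including questions on age, sex, career, means of transport, geographic area of residence, screen time, and socioeconomic level of the participants". Campus is not named.
- **Statistical Analysis.** After the final evaluations, within-group tests are run "along with the intergroup differences (Student *t* test or Mann-Whitney *U* test"). The adjusted analysis is an addition: "In addition, regression analyses will be performed incorporating the covariates".
- **Upper Body Muscle Strength and Body Composition.** One model is named per main instrument, without reference to campus. For grip: "Using a digital dynamometer (Takei T.KK.5401; Takei Scientific Instruments Co, Ltd), grip strength will be evaluated". Weight and bioimpedance use the Tanita MC-780U, and height the Seca 222.
- **Cardiorespiratory Fitness.** The test is a 20-m shuttle run paced by a recording. It stops when the participant misses the line twice in a row or cannot continue.

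**The concern.** Campus is the one structural grouping that the design creates itself. Student populations may differ between the three cities. Several outcomes also depend on who measures and where: someone must judge missed lines in the shuttle run, waist is taken between skin marks, and skinfolds depend on the operator. Campus may therefore account for part of the outcome variance.

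No step described in the article deals with that part. The t or Mann-Whitney comparison leaves it in the error term, and the regression is described with a covariate list that does not name campus. If allocation is not stratified, the campus mix of the two arms will also differ by chance, and the stated test does not correct for it.

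At stake is the precision of the main comparison, plus the consistency of repeated measurements if a student could be tested on different units at baseline and at the end.

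**Working it through.** **1. The plan's own figure.** Sample Size Calculation gives a difference of 3, SD 5, α 0.05, power 0.80 and 99 per group. Sidedness is not stated there; two-sided is assumed.

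n per group = 2 × (1.960 + 0.842)² × SD² / difference² = 2 × 7.849 × 25 / 9 = 43.6, so 44.

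The stated 99 is not reproduced. It is what a difference of 2 gives: 2 × 7.849 × 25 / 4 = 98.1, so 99. That is a separate matter, but it decides how much spare power there is, so both differences are carried below.

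**2. Chance imbalance if allocation is not stratified.** Assumption: 66 students per campus (198 / 3), with 99 of 198 allocated to each arm. The number of a campus's students in the intervention arm is then hypergeometric, with mean 33, SD 3.3 and a 95% range of 27 to 39. A campus's share differs between arms by at least 10 percentage points when |2a − 66| / 99 ≥ 0.10, that is, when its count a is at least 5 away from 33. Summed exactly over all allocations, this happens for at least one campus in about 36% of them. A difference of 20 points or more occurs in about 1%.

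**3. The same imbalance in outcome units.** Suppose campus means differ by −2, 0 and +2 around a residual SD of 5.

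- Campus variance = (4 + 0 + 4) / 3 = 2.67, a share of 2.67 / (2.67 + 25) = 9.6%.
- SD of the chance shift in the group difference = √(2.67 × 198/197 × 2/99) = 0.23. In simulation its mean was 0 and the 95th percentile of its absolute value was 0.44.
- With offsets of −1, 0 and +1 (share 2.6%), the SD is 0.12 and the 95th percentile 0.22.

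These compare with a stated target difference of 3. The simulated type I error of the unadjusted test was 5.1% with the smaller offsets and 5.2% with the larger.

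**4. Precision.** If campus explains a share R² of the outcome variance, the ratio of the unadjusted to the adjusted standard error is about 1/√(1 − R²). The equivalent sample is 198 × (1 − R²).

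| R² (assumed) | SE ratio | Equivalent n of 198 |
|---|---|---|
| 1% | 1.005 | 196 |
| 5% | 1.026 | 188 |
| 10% | 1.054 | 178 |
| 20% | 1.118 | 158 |

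Adjusting after unstratified allocation has a small price of its own: with three campuses of 66, simulation gives an average rise of about 1% in the variance of the estimate. The gain is therefore roughly nil if campus explains only 1%.

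**5. Power at 99 per arm.** The effect depends on whether the planning SD of 5 already contains campus variance.

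| R² | SD 5 is total, campus adjusted: diff. 3 / diff. 2 | SD 5 is within campus, campus ignored: diff. 3 / diff. 2 |
|---|---|---|
| 0 | 98.8% / 80.4% | 98.8% / 80.4% |
| 5% | 99.1% / 82.3% | 98.4% / 78.3% |
| 10% | 99.4% / 84.3% | 98.0% / 76.1% |
| 20% | 99.7% / 88.2% | 96.5% / 71.1% |

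For the stated difference of 3, the largest loss is 98.8 − 96.5 = 2.3 points. For a difference of 2 it is about 9 points, and only if SD 5 excludes campus variance.

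**The case against.** The case against is substantial, and much of it stands.

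- **Randomisation.** A reader might infer that allocation ignores campus and runs from one undivided list. The article does not say so. It names the software and the two groups and refers to a flowchart that is not shown. Stratification and blocking are details that an article may leave to the full protocol.
- **Devices.** A reader might infer that devices differ between campuses. No section says so, and the measurement sections name a single model per main instrument. The sample-size outcome is a field test that depends on no measuring device. What remains is possible variation in unit, setting and evaluator. The Results section says that evaluators will be trained from September to December 2025, which should reduce the last of these.
- **Same campus at both tests.** The natural reading of Participants is that each student is tested at their own campus, at the start and at the end.
- **Partial adjustment.** Area of residence is a listed covariate and may partly stand in for campus, and the list opens with the word *including*. The proxy is undefined, however, and enters only the additional regression.
- **Cancellation in change scores.** A constant campus offset drops out of within-person change. This helps only if the arms are compared on change, and Statistical Analysis does not say whether the between-group test uses change or final values.
- **Bias.** Calling the effect bias would be wrong. Randomisation of individuals keeps the comparison unbiased, and the type I error is essentially nominal.

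**Conclusion.** The point holds as a modest matter of precision and clarity. Outcomes are collected at three campuses, the stated between-group test is unadjusted, and the listed covariates do not include campus. Nothing described in the article therefore removes campus variation from the comparison. The standard error would be about 3%, 5% or 12% larger than necessary if campus explained 5%, 10% or 20% of the outcome variance. Those shares are assumptions, and so are the equal campus sizes behind the imbalance figures.

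The validity of the trial is not in question. Even with campus offsets of −2, 0 and +2, the chance shift has an SD of about 0.23 against a target of 3. For that target the power loss is at most 2.3 points within the range examined. It would matter more, up to about 9 points, if the real design difference is 2 and the planning SD excludes campus variance.

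The wording on equipment in Participants and the single named models in the measurement sections are compatible, but should be tied together explicitly.

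**What to change.** 1. **Statistical Analysis and Covariables:** add campus as a fixed factor in the between-group regression, and report that adjusted estimate. Cost: two degrees of freedom.
2. **Randomization:** state whether allocation is stratified by campus. If it is not, generate the EPIDAT list separately within each campus, in blocks, and keep campus in the model. Cost: three lists instead of one. This must be settled before allocation starts, because it cannot be repaired afterwards.
3. **Participants:** replace the general reference to local equipment with a statement that the models named under Upper Body Muscle Strength and Body Composition are used at every campus. Add that each participant is tested at the same campus and on the same unit at baseline and final evaluation. Cost: a sentence in the protocol and a minor scheduling constraint at the final tests.

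No additional participants or procedures are needed.

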### Randomization

This study will adopt a single-blind RCT design. Using EPIDAT software (version 4.2; Pan American Health Organization), participants will be divided into 2 groups (ie, group 1 [intervention] and group 2 [control]).

### Sample Size Calculation

On the basis of what was proposed for the design of the RCTs [27], the number of participants will be calculated. Taking 2 RCTs that aimed to increase physical activity levels through walking [18,19] as reference, the sample will be calculated considering an absolute difference of 3% (α error of .05 and statistical power of .80) between the intervention group and the control group in the mean percentage of cardiorespiratory endurance (SD 5), giving a required sample of 99 participants for each group (intervention and control).

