### Measuring Health Indicators

#### Cardiorespiratory Fitness

This indicator will be measured through the 20-m shuttle run test [31]. Participants must run between 2 lines separated by 20 m. The speed at which they must move is indicated by a sound emitted by a recorded tape. The participant begins at a speed of 8.5 km/h, which increases by 0.5 km/h every minute. When a participant being evaluated fails to reach the lines twice in a row, along with the sound, or when they are unable to continue running the test, the evaluation is completed, and the minute reached is recorded. According to the proposal, the maximum oxygen consumption is estimated [31].

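### The stated inputs (difference 3, SD 5, alpha .05, power .80) give 44 to 45 participants per group, not the stated 99, and the article does not show which figure is misstated

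*Protocol article*

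**What the plan says.** The Sample Size Calculation section names two earlier walking trials as its reference and sets the target as follows: "the sample will be calculated considering an absolute difference of 3" per cent, with "α error of .05 and statistical power of .80", "in the mean percentage of cardiorespiratory endurance (SD 5), giving a required sample of 99 participants for each group". The figure of 99 per group is presented as the direct result. The section mentions no allowance for dropout, clustering or multiple outcomes.

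The Methods paragraph of the Abstract repeats the figure for each arm: "An intervention group (n=99) and a control group (n=99) will be randomly selected".

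The Statistical Analysis section compares the groups with a "2-tailed Student *t* test or Mann-Whitney *U* test". The two-tailed label is attached to the baseline comparison; the final between-group comparison uses the same pair of tests.

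Under Cardiorespiratory Fitness, the measurement is the 20-m shuttle run: "the minute reached is recorded. According to the proposal, the maximum oxygen consumption is estimated". No percentage is defined there.

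**The concern.** The paragraph prints a full set of inputs and an answer, so it can be checked directly, and the answer is about 2.2 times what the inputs require. It is the only justification the article gives for the size of the trial.

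The possible corrections describe different trials. With the printed difference and SD, 99 per group is far more than 80% power needs and leaves ample room for loss. If the standardised difference intended was about 0.40, 99 per group reaches 80% only with complete data. As written, a reader cannot tell which effect the trial was designed to detect, or which effect a null result would speak against.

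**Working it through.** **Inputs.** From Sample Size Calculation: difference 3, SD 5, alpha .05, power .80, two groups, 99 per group. From the Abstract: equal arms of 99. Sidedness is not stated in the sample size section; two-sided is taken as the base case from the Statistical Analysis section, and one-sided is tried as well.

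**Attempt to reproduce 99.** For two independent means,

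n per group = 2 × (z₀.₉₇₅ + z₀.₈₀)² × SD² / difference²

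- (1.960 + 0.8416)² = 7.849
- n = 2 × 7.849 × 25 / 9 = 43.6, so 44 per group
- Noncentral t: 44.6, so 45 per group

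The stated 99 is not reproduced: 99/45 = 2.2.

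**Variants that keep difference 3 and SD 5 (per group).**

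| Variant | n per group |
|---|---|
| One-sided, power .80 | 35 (normal), 36 (t) |
| Two-sided, power .90 | 59 (normal), 60 (t) |
| Two-sided, power .95 | 73 (normal), 74 (t) |
| Mann-Whitney efficiency .955 to .864 | about 47 to 51 |
| Bonferroni for 10 outcomes, power .80 | 74 |
| Uncorrelated change score, SD 5√2 | 88 |

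Inflation for dropout would need a loss of 1 − 44/99 = 55.6% (or 1 − 45/99 = 54.5%). A total of 90 inflated for 10% loss is 90/0.9 = 100, which is close to 99 as a total, but the text gives 99 for each group and states no loss rate.

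**Power of 99 per group at the printed inputs.** Noncentrality = 0.6 × √(99/2) = 4.22. Power is 98.8% (normal) or 98.7% (t).

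**What 99 per group does correspond to at two-sided .05 and 80% power.** Standardised difference = 2.8016 × √(2/99) = 0.398.

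- With SD 5, the difference is 0.398 × 5 = 1.99. Forward check: 2 × 7.849 × 25 / 4 = 98.1, so 99 (t solution 99.08).
- With difference 3, the SD is 3 / 0.398 = 7.53. Forward check with SD 7.5: the standardised difference is again 0.40, so 98.1, that is 99.

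These two fit equally well. There are other routes: keeping difference 3 and SD 5 but using alpha .01 and power .95 also gives 99 by the normal formula, against the printed alpha and power. The arithmetic alone does not identify the wrong input.

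**Consequences under the two main readings (unadjusted two-sided t test).** The loss rates are illustrative, because the article gives none.

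| Loss | Analysed per group | Power, standardised difference 0.60 | Power, standardised difference 0.40 |
|---|---|---|---|
| 0% | 99 | 98.7% | 80.0% |
| 10% | 89 | 97.8% | 75.6% |
| 20% | 79 | 96.3% | 70.5% |
| 30% | 69 | 93.8% | 64.5% |

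**The case against.** The strongest case on the other side accepts the arithmetic and limits what follows from it.

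- **A reader might infer that the target was really a difference of 2.** The match is neat, but an SD of about 7.5 with the printed difference of 3 fits just as well, and a misreported power or an unreported inflation is also possible. The article favours none of these.
- **A reader might infer that the trial is underpowered.** The document does not show that. On the printed inputs, power stays at 93.8% even after 30% loss. The lower figures depend on a standardised difference of 0.40 that is printed nowhere. They also assume an unadjusted test; the planned regression with covariates could recover some power, although the baseline value of the outcome is not among the listed covariates.
- **A reader might infer that the SD of 5 belongs to no endpoint the trial measures.** That goes too far. The Procedures section uses cardiorespiratory endurance for the assessment that the shuttle run provides, and a percentage, such as a percent change, can be derived from it. What remains is an ambiguity of units that needs a short clarification.
- **The missing dropout allowance is not a defect in itself.** A condensed article may leave it to the full protocol. It counts here only because nothing in the text explains 99 as an inflated figure.

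All four limits stand. None of them makes the printed sentence true: the inputs and the result are both given and contradict each other, and a fuller document elsewhere would not change that.

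**Conclusion.** The sample size statement is wrong as written. Difference 3, SD 5, two-sided alpha .05 and power .80 need 44 (normal) or 45 (t test) per group. The stated 99 is 2.2 times the t-test figure, or 198 − 90 = 108 more participants in total, and gives about 98.7% power instead of 80%. This assumes two independent groups of equal size, a common SD and a two-sided test; a one-sided test moves the answer further from 99.

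At least one of the difference, SD, power or sample size is misstated, or an inflation is unreported. The document does not show which. The demonstrated harm is a power statement that cannot be interpreted. A shortfall in power is only conditional: it arises if the intended standardised difference was about 0.40 and participants are lost. It should be corrected, since the trial's size rests on this paragraph.

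**What to change.** Keep 99 per group and rewrite the paragraph from the original calculation. The inputs should not be chosen because they return 99.

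1. Recover the calculation and correct whichever input was misreported (difference, SD or power). State sidedness and any inflation used.
2. Restate the power that 99 per group gives, with and without loss:
   - If the printed inputs are right: 45 per group are needed; 99 gives 98.7% power, and 96.3% after 20% loss.
   - If the standardised difference is really 0.40: 80% power with complete data, and about 70% after 20% loss under an unadjusted t test. Replace the illustrative 20% with the sponsor's own expected rate.
3. Say whether the percentage and its SD refer to estimated maximum oxygen consumption, shuttle-run minutes or a percent change, so that the inputs are in the units of the analysed endpoint.

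The cost is one reworded paragraph and no additional participants. A stated figure may look less favourable once it is corrected.
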